### Recruitment

Recruitment will be performed within the pediatric clinics of the participating centers. Both referred and in-house patients will be approached after routine examination was performed. Eligible patients and their parents will receive the study information and consent forms. Written consent will be given by the parents of the children. There will be a minimum time period of 48 hours between receipt of study information and consent.

### Allocation and blinding

If more than one primary molar is eligible, the decision as to which tooth will be included into the study will be performed using random number tables (WH) before treatment is commenced. Sequence generation will be performed after inclusion via random number tables (WH). Allocation will be performed via sealed opaque envelopes after the six-monthly recall examination (six months after selective excavation) by the treating dentists. Thus, both the first excavation step and the first re-examination will be performed blinded as to whether further excavation will be performed or not. Clinical follow-up examinations will also be performed blinded to treatment group allocation. Blinding during the second excavation step and blinding of patients as to which treatment was performed will not be possible, but patients will be informed not to reveal treatment allocation to the examiner during follow-up examinations.

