## Methods/Design

### Overview

The planned study is a secondary care-based prospective, multicenter, two-arm parallel-group, randomized controlled trial at three pediatric university dental clinics in Germany: the Charité - Universitätsmedizin Berlin, the Ernst-Moritz-Arndt University Greifswald and the RWTH University of Aachen. We plan to enroll 300 patients with one or more deeply carious, sensitive and non-symptomatic deciduous molar. One molar per patient will be randomly allocated to receive one of two treatments (selective or stepwise excavation). The total follow-up time will be three years after completion of the initial treatment. Success, survival and restoration integrity will be assessed after one, two and three years. Patients’, parents’ and dentists’ preference will be assessed after each treatment using visual analogue or Likert rating scales. Costs will be assessed for the initial and follow-up treatments and will be based on a micro-costing approach. The study has been approved by the ethics committee of the Charité - Universitätsmedizin Berlin (approval number: EA4/057/14), the Ernst-Moritz-Arndt University Greifswald (approval number: BB 112/14) and the RWTH University of Aachen (approval number: EK 283/14). The study is registered at Clinicaltrials.gov (identifier: NCT02232828).

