### Sample size

The required sample size was calculated based on the primary outcome parameter, success (see below). We anticipate a hazard ratio of 1.3 [21] of stepwise excavated compared with selectively excavated teeth. If α = 0.05 and 1-β = 0.9, a sample size of n = 66 per group is required. Assuming an annual drop-out rate of 20%, 114 patients per group will be required. The total required sample size would thus be n = 228. To allow possible subgroup analyses, a total of 300 patients will be recruited (n = 100 per center).

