### Data analysis and statistical evaluation

The statistical evaluation will be performed using SPSS 20.0. Descriptive statistics will be calculated according to distribution of data. Log rank tests will be used to compare success and survival between groups, with effects of possible confounders (age, gender, dental anxiety, cooperation, use of local anesthetics, caries risk, dental arch, first or second molar, surfaces and center) being assessed. Moreover, we will use two-sided independent t tests or Mann-Whitney U test (to compare visual analogue scale results and costs) as well as chi-square tests (to compare restorative integrity and subjective grading of treatments).

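### The secondary comparisons (costs, visual analogue scores, grades, restoration integrity) use plain two-group tests that ignore center, which gives away precision at no saving; balancing the allocation by center is a smaller, optional addition.

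*Protocol article*

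**What the plan says.** The Overview describes a "randomized controlled trial at three pediatric university dental clinics in Germany", and under Sample size "a total of 300 patients will be recruited (n = 100 per center".

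Under Data analysis and statistical evaluation, success and survival are compared by log-rank tests. The same sentence gives a list of ten possible confounders that ends with "first or second molar, surfaces and center) being assessed". The next sentence fixes the secondary tests: "two-sided independent t tests or Mann-Whitney U test (to compare visual analogue scale results and costs"), and chi-square tests for restoration integrity and the subjective grades. That sentence mentions neither center nor any other covariate.

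Under Allocation and blinding: "Sequence generation will be performed after inclusion via random number tables". Then: "Allocation will be performed via sealed opaque envelopes after the six-monthly recall examination", opened by the treating dentists. The article mentions no blocks, strata, minimization or separate lists per center.

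**The concern.** The plan treats center as worth examining for the primary outcome and then drops it for the outcomes where it may well matter. Under Outcomes, costs are built from staff time, number of personnel and transportation. Ratings come from children, parents and dentists. Each clinic treats and documents its own patients. Differences between clinics in such measures are plausible, although the article does not report any.

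If center does affect an outcome, a two-group test counts the differences between clinics as random error. The error rate is kept, but intervals are wider and power is lower than the same data could give. The allocation, as described, also does nothing to equalize the arms within a clinic, so the center mix of the arms can differ by chance.

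**Working it through.** The plan gives no figure for a center effect or for within-center balance, so there is no stated result to reproduce. Its inputs are 3 centers, 100 children each (3 x 100 = 300), 1:1 allocation (implied by equal numbers per group) and 20% annual drop-out. Every center effect below is an assumption.

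**1. Precision lost by leaving center out of a secondary test.** If center explains a share R² of the outcome variance, the unadjusted standard error exceeds the center-adjusted one by the factor 1/√(1 − R²). The two degrees of freedom spent on center are negligible here. A comparison with 80% power unadjusted would, with center included, have power Φ(2.80/√(1 − R²) − 1.96), where 2.80 = 1.96 + 0.84.

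| Assumed R² | Standard error factor | Variance factor | Power, from 80% |
|---|---|---|---|
| 2% | 1/√0.98 = 1.01 | 1.02 | 81% |
| 10% | 1/√0.90 = 1.05 | 1.11 | 84% |
| 20% | 1/√0.80 = 1.12 | 1.25 | 88% |

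These gains come from the analysis. Balancing the allocation and then running an unadjusted t test would not deliver them.

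**2. Imbalance if the sequence is simple randomization.** With 100 children in a center, the difference between arm counts has standard deviation √100 = 10. The exact binomial probability of a 60:40 split or worse is 5.7% in one center, and 1 − (1 − 0.057)³ = 16% in at least one of three.

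**3. What that imbalance costs.** With x children in one arm of a center, efficiency relative to a 50:50 split is x(100 − x)/2500.

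- A 60:40 split gives 60 x 40/2500 = 0.96, a loss of 4% in that center.
- On average, E[x(100 − x)] = 100 x 99/4 = 2475, so efficiency is 2475/2500 = 0.99, a loss of 1.0%.
- In a simulation of three centers of 100, the 5th percentile of overall efficiency was 0.974, a loss of 2.6%.

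Once center is in the analysis, balanced allocation therefore adds about 1 to 2%.

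**4. Size for a binary outcome analyzed without center.** If the 20% annual loss applies from entry, about 300 x 0.8^0.5 = 268 children reach allocation at six months. Assume failure of 20, 30 and 40% in the three centers.

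- The variance between centers is 0.0067. Chance center mix contributes a standard deviation of √(4 x 0.0067/268) = 0.010 to the arm difference, a 95% range of about ±2 percentage points.
- Ordinary sampling error is already 1.96 x √(4 x 0.21/268) = 0.11, or ±11 points.
- Center then explains 0.0067/0.21 = 3% of the variance, and leaving it out widens the standard error by about 1.6%.

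**The case against.** The strongest reply is that this is a condensed article. Random number tables are a source of randomness and can be used to build permuted blocks, so the text neither states nor excludes blocks or center lists. Covariates for secondary tests are often left to an analysis plan. Simple randomization of 300 children is unbiased and keeps the error rate. It is also the least predictable scheme, which matters when treating dentists open the envelopes. Operating dentists are calibrated on the excavation criteria.

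Most of this stands, and it limits the point on allocation to a conditional, optional request. It does not dispose of the point on analysis, because the article names the secondary tests and those tests omit center. The calibration described concerns excavation criteria on extracted teeth, so it does not address costs or ratings.

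A reader might infer several stronger claims that the text does not support:

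- **That center drives re-intervention decisions and costs.** The Discussion says only that the need to re-intervene is judged subjectively, and Outcomes lists cost components. Neither compares clinics.
- **That noise enters every comparison.** Center is among the factors to be assessed with the log-rank tests for success and survival.
- **That the increase to 300 was meant for center or surface subgroups.** Sample size refers to possible subgroup analyses and names none.

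**Conclusion.** The point holds as one of precision. The stated secondary tests are valid but less precise than they need be, by about 1, 5 or 12% of the standard error if center accounts for 2, 10 or 20% of the variance. Those shares are assumptions; if the true share is near 2%, the gain is negligible. For success and survival the plan already intends to look at center, but it does not say that the test itself will be stratified.

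It would be tempting to conclude that the allocation method is the main fault, or that it biases the comparison. The figures do not support this. Chance imbalance causes no bias on average, and the benefit of balancing is about 1 to 2% once center is in the analysis. Whether the sequence is in fact unbalanced cannot be settled from the article.

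**What to change.** **Main change, under Data analysis and statistical evaluation.** Carry center in the secondary comparisons: a linear model with arm and center for costs and visual analogue scores, and a center-stratified rank or ordinal test for grades and restoration integrity. For success and survival, make the log-rank test stratified by center. This takes a sentence or two in the analysis section. It needs no extra patients or data, since center is known for every child, and it can still be adopted if the sequence can no longer be changed.

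**Optional change, under Allocation and blinding.** If the full protocol already balances by center, say so. If not, generate the sequence separately for each center in permuted blocks of varying, undisclosed size, used in the order in which envelopes are opened at the six-month visit. The cost is a short script and envelopes labelled by center. The small downside is that dentists who open envelopes might guess block ends, so block sizes must vary and stay undisclosed.

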### Outcomes

Outcomes will be assessed by the treating dentists or study nurses. The primary outcome of the study will be success (not requiring any re-intervention). Secondary outcomes will include survival (not requiring extraction), restoration integrity, assessed via modified USPHS-criteria [13], patients’ subjective assessment of the treatment using a visual analogue scale (for stepwise excavation, assessments will be performed twice and mean visual analogue scale results will be calculated), dentists’ and parents’ subjective assessment of the treatment using grades 1 (very good) to 6 (very bad) and initial and follow-up treatment costs (calculated by combining costs for staff, as assessed by time required for the procedures and the number of personnel involved, and costs for transportation of patients or materials).

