### Setting and participants

The study will take place in three dental university clinics in Eastern, Northern and Western Germany. All are publically funded teaching hospitals. We will include children aged between three and nine-years-old with a minimum of one sensitive, clinically and radiographically non-symptomatic, retainable, deeply carious deciduous molar with a caries lesion involving either only the occlusal or the occlusal and exactly one proximal (mesial or distal) surface. The lesion will be required to radiographically extend into the inner third of the dentin (D3) and show signs of activity, such as plaque retention, papillary bleeding and/or softness of the surface [20]. Patients will require parental consent for participation. In addition, patients’ cooperation for treatment under no or only local anesthesia will be expected.

Patients participating in another study, patients with parents planning to move away within the next three years, patients who are not residents of the federal states of Berlin, Brandenburg, Mecklenburg-Vorpommern and Nordrhein-Westfalen, as well as patients with systemic diseases or disabilities will not be included. Patients with known allergies to dental materials used within the study as well as those with teeth expected to exfoliate within the next 18 months will also not be included.

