### Intervention and data collection

In the first visit, a full assessment and intraoral examination will be performed. For patients who are possibly eligible, caries risk will be estimated [22] and dental anxiety assessed [23]. If informed consent is given, treatment will be provided in the second visit, with local anesthetics being applied according to individual needs. Removal of enamel and cavity preparation will be performed using water-cooled diamond instruments. Caries removal in the periphery including the enamel-dentinal junction will be performed using rose head burs and/or an excavator until hard, dry dentin remains. Pulpo-proximal caries will be removed until leathery, slightly moist and reasonably soft dentin remains. Operating dentists will be calibrated prior to study commencement regarding these criteria using extracted teeth. Moisture control will be performed using cotton rolls and continuous aspiration. Restoration will be performed adhesively with the use of a self-etching one-bottle adhesive (G-aenial bond, GC, Bad Homburg, Germany) and a compomer material (Dyract, Dentsply Detray, Konstanz, Germany).

After six months, a follow-up examination will be performed. After the examination, allocation will be revealed. If allocated to stepwise excavation, the second excavation will be performed as described until only hard, dry dentin remains. Restoration will again be provided adhesively as described. All treatment steps will be documented photographically if possible (Figure 1).

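### The child's visual analogue score is compared between arms without adjustment for age and dental anxiety, both recorded before treatment; the planned test is valid but gives up precision of unknown size

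*Protocol article*

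**What the plan says.** All places are in the protocol article.

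- **Outcome.** Outcomes lists the child's "subjective assessment of the treatment using a visual analogue scale" as secondary. It adds that "for stepwise excavation, assessments will be performed twice and mean visual analogue scale results will be calculated". Objectives and hypotheses includes a difference in patients' preference among the secondary hypotheses.
- **Test.** Data analysis and statistical evaluation fixes "two-sided independent t tests or Mann-Whitney U test (to compare visual analogue scale results and costs". No covariate is attached to this comparison.
- **Where covariates appear.** The same paragraph has "Log rank tests will be used to compare success and survival between groups, with effects of possible confounders (age, gender, dental anxiety" and further factors. That list belongs to the time-to-event comparisons only.
- **When the covariates are recorded.** Intervention and data collection states that at the first visit "caries risk will be estimated [22] and dental anxiety assessed [23". Table 2 marks dental anxiety and demographics as preoperative. Setting and participants makes age an eligibility criterion: "children aged between three and nine-years-old".
- **When allocation takes place.** Allocation and blinding states: "Allocation will be performed via sealed opaque envelopes after the six-monthly recall examination".

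**The concern.** A three-year-old and a nine-year-old, or a calm child and a frightened one, may well rate the same dental session differently. If so, age and anxiety account for part of the spread of the score. A two-sample test leaves that part in the error term, and the confidence interval is wider than the collected data allow. The article already treats both variables as relevant to success and survival, yet does not use them for a rating in which their influence is at least as plausible.

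At stake is the precision of one secondary comparison, the one that carries the hypothesis on children's preference. Neither the primary outcome nor the sample size is affected.

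**Working it through.** **Is there a figure to reproduce?** None for this outcome. Sample size states "If α = 0.05 and 1-β = 0.9, a sample size of n = 66 per group is required", but that calculation is for success. No standard deviation, difference or power is given for the visual analogue score, so the gain can only be shown over an assumed range.

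**Are the covariates usable?** Both are recorded before the first treatment, and allocation is revealed only after the six-month recall. Neither can be influenced by the arm, so conditioning on them introduces no bias.

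**Inputs**
- From the article: 300 children. Equal arms of 150 are an assumption, because the ratio is not stated.
- Assumed: R², the share of the variance of the score explained by age and anxiety, from 0 to 0.25.
- Assumed for reference: a comparison that would have 80% power unadjusted, two-sided at 0.05 (noncentrality 1.96 + 0.84 = 2.80).

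**Formulas (linear model, similar spread in both arms)**
- Standard error ratio, adjusted to unadjusted: √(1 − R²)
- Equivalent sample size: 1/(1 − R²)
- Power: Φ(2.80/√(1 − R²) − 1.96)
- Difference detectable with 80% power at 150 per arm, in SD: 2.80 × √(2/150) × √(1 − R²)

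| Assumed R² | SE ratio | Worth in children | Power (80% unadjusted) | Detectable difference |
|---|---|---|---|---|
| 0 | 1.000 | +0% | 80% | 0.323 SD |
| 0.05 | 0.975 | +5% | 82% | 0.315 SD |
| 0.10 | 0.949 | +11% | 84% | 0.307 SD |
| 0.20 | 0.894 | +25% | 88% | 0.289 SD |
| 0.25 | 0.866 | +33% | 90% | 0.280 SD |

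For example, at R² = 0.10: 2.80/0.949 = 2.95, less 1.96 is 0.99, and Φ(0.99) = 84%. At 0.25: 2.80/0.866 = 3.23, less 1.96 is 1.27, and Φ(1.27) = 90%.

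**Check by simulation, normal scores.** With 134 per arm (150 × 0.8^0.5, six months of loss at 20% a year) and an assumed difference of 0.3 SD, power was:

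| R² | t test | Mann-Whitney | Linear model with covariates |
|---|---|---|---|
| 0 | 68% | 66% | 68% |
| 0.10 | 70% | 68% | 74% |
| 0.20 | 68% | 66% | 78% |

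At R² = 0 the adjustment costs practically nothing.

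**Check by simulation, skewed scores.** The article allows the Mann-Whitney test, the natural choice if ratings are skewed. For an assumed right-skewed 0 to 100 score (134 per arm, 0.3 SD and R² on the latent scale), power was:

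| Latent R² | Mann-Whitney | Linear model with covariates, robust SE |
|---|---|---|
| 0 | 67% | 59% |
| 0.10 | 68% | 64% |
| 0.15 | 65% | 63% |
| 0.25 | 66% | 67% |

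A second simulation at R² = 0.10 gave 67% for Mann-Whitney, 63% for the adjusted linear model and 72% for an adjusted rank-based model. With scores of this shape, replacing the rank test by a linear model of means loses power over most of the range, whereas adjusting on the rank scale gains it.

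**The case against.** The strongest reply is that nothing here is wrong. Under randomisation the unadjusted test has the right type I error and its interval the right coverage, and a chance imbalance in age or anxiety is ordinary sampling error that the interval already covers. That stands. A reader might infer that the planned comparison is biased or confounded, and the documents do not support that.

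The size is also open. No correlation between age or anxiety and the score is given, so R² could be near 0.05, worth 5% more children, or zero. A reader might conclude that a definite amount of precision is being thrown away; only a conditional range can be shown.

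Third, a linear model is not always better than the planned analysis. Against the Mann-Whitney test with skewed scores it can lose power, and it changes the target from a rank comparison to a mean difference. That stands too, and it is why the remedy has to follow the shape of the score.

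It could also be said that adjusted secondary analyses are a matter for a statistical analysis plan. This has less force, because the article does not leave the method open: it names the tests for this outcome and attaches the covariates elsewhere.

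**Conclusion.** The point holds as a free but modest improvement to a stated method. The child's score is tested without covariates although age and dental anxiety are available for every enrolled child before allocation. The test is valid and the loss is one of precision on a secondary outcome. Its size rests wholly on an assumed R²: equal to 0% more children at R² = 0 and 33% more at 0.25, with 80% power becoming at most about 90%. These figures assume a linear model and roughly normal scores.

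A reader might also infer that adjustment puts the comparison of children's ratings in order. It does not. In the selective arm the score is a single rating made before allocation is revealed. In the stepwise arm it is the mean of that rating and one made after the second excavation, so any effect of the second step on the rating is halved. Adjusting for age and anxiety only narrows the interval around that contrast. The definition of the score is a separate problem and needs its own solution.

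**What to change.** In Data analysis and statistical evaluation, pre-specify a model of the child's visual analogue score on arm, preoperative dental anxiety and age:

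- where the t test would have been used, a linear model with robust standard errors, reporting the adjusted mean difference with its 95% confidence interval;
- where the Mann-Whitney test would have been used because scores are skewed, a covariate-adjusted rank-based model or an ordinal (proportional-odds) model.

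The cost is a sentence or two of text and a little more analysis work. No new data, visits or children are needed. If the covariates are not prognostic, the loss of power is negligible provided the model suits the shape of the score. The two-rating versus one-rating definition in Outcomes should be settled separately.

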### Intervention and data collection

In the first visit, a full assessment and intraoral examination will be performed. For patients who are possibly eligible, caries risk will be estimated [22] and dental anxiety assessed [23]. If informed consent is given, treatment will be provided in the second visit, with local anesthetics being applied according to individual needs. Removal of enamel and cavity preparation will be performed using water-cooled diamond instruments. Caries removal in the periphery including the enamel-dentinal junction will be performed using rose head burs and/or an excavator until hard, dry dentin remains. Pulpo-proximal caries will be removed until leathery, slightly moist and reasonably soft dentin remains. Operating dentists will be calibrated prior to study commencement regarding these criteria using extracted teeth. Moisture control will be performed using cotton rolls and continuous aspiration. Restoration will be performed adhesively with the use of a self-etching one-bottle adhesive (G-aenial bond, GC, Bad Homburg, Germany) and a compomer material (Dyract, Dentsply Detray, Konstanz, Germany).

After six months, a follow-up examination will be performed. After the examination, allocation will be revealed. If allocated to stepwise excavation, the second excavation will be performed as described until only hard, dry dentin remains. Restoration will again be provided adhesively as described. All treatment steps will be documented photographically if possible (Figure 1).

